## Abstract

**Background:**

In Germany, advance care planning (ACP) was first introduced by law in 2015. However, ACP is still uncommon in Germany and only few people have advance directive forms. This study aims to evaluate an ACP program in care dependent community-dwelling persons, compared to optimised usual care.

**Methods:**

A cluster-randomised controlled trial of 12 months duration will be conducted in 3 German study sites comparing the pretested ACP-counselling offered by trained nurses with a control group receiving optimised usual care. Using external concealed randomisation, 16 home care services each will be included in the intervention and the control group (30 participants per cluster; *n* = 960). Eligibility criteria for patients are: ≥60 years, somehow care dependent, adequate German language skills, assumed life-expectancy of ≥4 weeks, and cognitive ability for participation.

ACP will be delivered by trained nurse facilitators of the respective home care services and communication will include proxy decision-makers. The primary endpoint will be patient activation, assessed by the Patient Activation Measure (PAM-13). Secondary endpoints include ACP-engagement, proportion of prepared advance directives, number and duration of hospitalisations, quality of life as well as depression and anxiety. Further, comprehensive economic and process evaluations will be conducted.

**Discussion:**

STADPLAN is the first study in Germany that assesses an adapted ACP intervention with trained nurses in home care services and the first international study focusing on cost effectiveness of ACP in community-dwelling older persons. The results will help to improve the understanding and communicating of patients’ preferences regarding medical treatment and care and thereby contribute to patients’ autonomy.

**Trial registration:**

German Clinical Trials Register: DRKS00016886 (Date of registration: 04.06.2019).

## BACKGOUND

Worldwide demographic changes lead to increased numbers of care dependent and chronically ill older persons [1, 2]. Functional and cognitive impairment are often accompanied by multimorbidity as well as nursing home admissions and frequent hospital stays [3–5]. Furthermore, care dependency decreases life expectancy [6]. For Germany, the number of care dependent persons is estimated to rise from 3.4 million today [7] to over 4.5 million in 2050 [8], of whom most will be community-dwellers [9].

Shared decision making with respect to nursing and medical decisions as well as improved communication processes between patients and health care professionals are essential elements of high-quality care [10]. In Germany, shared decision making has been included in the Patients’ Rights Act “Patientenrechtegesetz” since 2013.

Therefore, the concept of advance care planning (ACP) has become increasingly important. ACP is a process of discussing in advance a person’s health care preferences and wishes regarding future treatment especially if – due to physical or mental deterioration – the person cannot state his or her wishes anymore [11]. The communication process takes place between individuals and specifically skilled facilitators such as nurses, social workers, or physicians and may also involve relatives.

Persons are encouraged to document their future treatment preferences in advance directives (AD) and update them regularly as health status and preferences might change over time. By these repeated conversations, health care professionals and relatives learn about a person’s priorities, beliefs, values, and choices and therefore are able to arrange treatment accordingly in potential future situations [11]. In this way, ACP extends a persons’ autonomy to a phase in life where he or she becomes incapacitated.

Although the German Advance Directives Act “Patientenverfügungsgesetz” of 2009 confirmed that ADs are binding and the prevalence has been rising during the last years, ACP is still not widely implemented in Germany [12]. Since 2015, the Act to improve Hospice and Palliative Care (“Hospiz- und Palliativgesetz”) stipulates that ACP in German nursing homes is funded by the health insurance funds. However, only few residents, have an AD and most fail to accurately state what should be done when the person acutely becomes incapable of participating in treatment decisions [13, 14]. A patient’s AD may also be disregarded by medical and nursing staff due to insufficient communication.

Therefore, successful ACP programs require a cross-sectoral, multidisciplinary approach, which implies improved communication even among all healthcare providers [15]. Studies from other countries have shown that ACP can reduce distress, depression and anxiety not only in residents but also in significant others and care staff [16, 17]. However, compared to optimised usual care, ACP programs have not been studied solely in community-dwellers [18, 19]. Therefore, no evidence is currently available on the effectiveness of ACP programs implemented by trained nurse facilitators in the home care setting. The cost-effectiveness of ACP is not well understood, although some evidence indicates that ACP is associated with healthcare savings in nursing home residents [20–22].

### Objective

The main focus of this study is to evaluate the effect of an ACP program on patients’ activation regarding healthcare issues, compared to optimised usual care in care dependent community-dwelling older persons.

Further aims are to assess the intervention’s impact on patients’ ACP engagement as well as prepared AD forms, hospitalisations and institutionalisations, anxiety and depression, self-reported health-related quality of life, and mortality. A process evaluation developed according to the MRC framework [23] will be performed to analyse the implementation process, mechanisms of impact and contextual factors that might influence the outcome of the intervention. A health economic evaluation will assess the cost implications of the intervention over 12-months of follow-up.

## Methods

### Study design and setting

STADPLAN (STudy on ADvance care PLANning in care dependent community dwelling older persons) is a two-arm cluster randomised controlled trial of 12-months follow-up, conducted to evaluate the effect of an ACP program compared to optimised usual care for people living at home receiving professional home care. Figure 1 summarises the process of enrolment, randomisation, and measurement points during follow-up.

**Fig. 1 Fig1:**
[figure not shown]
Study flow chart

### Preparatory work

The patient-centred ACP programme “Respecting Choices®” [24] was adapted to the home care setting and the German context (GM, AB, HL, ÄK). The intervention components were systematically adapted to the needs of community nursing care in Germany and guided by the Behaviour Change Wheel method [25]. Compared to the “Respecting Choices®” program, the adapted version is less time consuming and more feasible for nurses who will deliver the ACP counselling under “real-life” conditions. The aim is not only to prove effectiveness, but also feasibility and potential for future implementation within existing structures rather than setting up parallel new structures.

The adapted intervention of the STADPLAN study was piloted with four home care services (two each in Halle (Saale) and Oldenburg) in 2018. The pilot study included the whole intervention, the recruitment of home care services and patients, baseline measurements, and parts of the process evaluation up to 3 months after baseline measurement. It helped to optimise the feasibility regarding recruitment, as one result was to minimize the time required for participation. One result was, that the acceptability could be raised by means of decreasing the age from 65 to 60 as inclusion criterion, because the nursing services stated to find it relevant not to exclude the younger clients from information regarding ACP. Moreover, it was helpful to maximise the understanding of used forms like written information and the conversation guide as well as the acceptability of the intervention parts and organisational factors by getting direct feedback from the nurses.

### In- and exclusion criteria for home care services

In total, 32 home care services will be recruited throughout the catchment areas of the three study sites Lübeck, Oldenburg (both north western Germany) and Halle (Saale) (eastern Germany). Each home care service has to care for 70 patients or more and be willing to assign at least two key nurses for the ACP training as well as for the counselling conversations. Minimum qualification of the participating nurses is 3 year professional education (registered nurse) or a bachelor’s degree. Key nurses recruit participating patients and in the intervention group conduct the ACP counselling additionally. Home care services with mainly or solely special alignment, e.g. palliative, paediatric or intensive care will not be considered.

#### In- and exclusion criteria for patients

To be eligible, patients have to be (i) clients of a participating home care service, (ii) aged 60 years or older, (iii) assigned to a care grade of 1 or higher, and (iv) rated into a life-expectancy of at least 4 weeks. Furthermore, (v) adequate German language skills, and (vi) the cognitive ability to follow the intervention and data collection are required. The latter will be assessed using the stepwise approach of the Dementia Screening Scale (DSS), a validated seven-item proxy instrument for nurses where a score of “0” indicates no cognitive impairment and “14” the most severe cognitive impairment [26]. Patients with a total DSS score < 3 will be included in the study whereas those scoring between 3 and 5 will only be eligible if the respective key nurses consider them competent to follow the intervention and to give informed consent. No further exclusion criteria will be applied.

An expected mean of 30 patients are aimed to be included per home care service (*n* = 960 patients).

### Recruitment

A total of 288 home care services are located in the three study sites Oldenburg, Lübeck and Halle (Saale) [27]. Of those 32 (11%) will be recruited. The selected home care services will be invited to take part in the study via postal mail and subsequent telephone calls. This strategy has been successfully applied in previous studies conducted in nursing homes [28, 29] or home care services [30]. The recruitment process will be documented including dates, contact times, and feedback.

Interested home care services have to take part in three separate recruitment interviews provided by study assistants, following the structure presented in Fig. 1 and involving the key nurses, who will thereby be prepared for the standardised patient recruitment. Key nurses will prepare a list of all patients fulfilling the inclusion criteria. This list will be ordered randomly and subsequent patients will be asked for participation until 30 patients will be recruited.

### Randomisation

Randomisation will be carried out on the cluster level (i.e. the home care service) by one investigator ([name]), who is not involved in the recruitment process. Thus, allocation concealment will be guaranteed. Clusters will be allocated 1:1 between intervention and control group. Computer-generated lists will be used with block sizes of two in order to inform the home care services as fast as possible so they can reliably plan time for intervention. Each pair will be allocated simultaneously. Randomisation will be stratified by study site (Oldenburg, Lübeck and Halle (Saale)).

### Intervention and control

The STADPLAN study uses a complex intervention which was established in accordance with the UK Medical Research Council’s (MRC) guidance for developing and evaluating complex interventions [31]. Respecting Choices® was implemented in the United States since 1990 [32] and is conceptually based on the ethical principles of informed consent, best interest and shared decision making [17, 33]. The intervention will be conducted on two levels: (i) the home care service and (ii) the patient level (see Table 1).

**Table 1 Tab1:** Intervention elements of the STADPLAN study

Intervention group	Control group (optimised usual care)
**Home care service level**	
**2-day training for participating nurses** Divided into 7 modules: M1: Introduction of the STADPLAN study M2: Introduction of the topic ACP M3: Practical exercise of the counselling conversations, extensive practise of the guided conversations with partners using different health situations/cases M4: Facilitator’s tasks and schedule in the course of the study M5: Reflexion on conversation experiences M6: Special practical training of difficult conversational situations, refresher of knowledge on ACP M7: Feedback and closing of the training	**–**
**Patient level**	
**ACP counselling (divided into 2 parts)** **Part 1**: Information on the project, ACP, aim of the conversations, information on the tasks and features of the surrogate/ representative, information on the written living will, introduction of the written information brochure, preparation of the next conversation: topic and goal, presence of a representative, **Part 2**: Repeating information on project, ACP and aim of the conversation, introduction of the following topics: attitudes, preferences and values of the participant, reflection on the use of the additional written information and integration of notes, clarification: further conversations requested?	**–**
**Written information on ACP:** Information brochure of about 60 pages containing: • Introduction to ACP, surrogate decision making and advance directive documents • Presentation of critical health scenarios along with incapacity • Glossary of medical and legal terms, contact information on local consultancies	**Written information on ACP:** Brochure of about 15 pages containing: • Introduction to ACP, surrogate decision making and advance directive documents (condensed) • Presentation of critical health scenarios along with incapacity (condensed) • Glossary of medical and legal terms, contact information on local consultancies

*ACP* advance care planning, *BEVA* trained nurse facilitator

#### Intervention group

In a 2-days workshop, key nurses from the respective home care services will receive ACP training and be prepared for their role as facilitator (short German version: “BEVA”). This workshop will provide an introduction to ACP and inform about the possibilities for ADs. Further, BEVAs will train counselling conversations using the conversation guide developed in the STADPLAN study. Finally, conversation experiences and problems, as well as coping strategies will be discussed.

On the patient level, the intervention will include two components which consist of (i) a formal ACP counselling provided by the BEVA and (ii) a written information brochure. The first component, the ACP counselling, is divided into two counselling meetings at the patient’s home. The first conversation lasts about 30 min and follows the developed and pre-tested guideline (Table 1). The written information brochure will be delivered and explained during this first conversation. In a structured approach, this brochure encourages the discussion of health care preferences and wishes regarding future treatment in case a person cannot state his or her opinion anymore. It further includes a glossary of medical and legal terms as well as contact information on local consultancies. The second conversation is also based on a semi-structured guideline and lasts about 60 min. The patient’s proxy decision maker or another person of trust, if available, will be invited to take part.

Reasons for discontinuing intervention are withdrawing consent, death, or moving to a nursing home.

The intervention’s primary aim is to promote patients’ awareness of ACP and their activation with respect to future treatment preferences. It also supports the conversation between patients and their proxy about wishes and treatment aims and motivates to this process to be able to take into account future changes or modifications of the patients’ wishes. The completion of AD forms is not part of the intervention.

#### Control group

Patients in the control group will receive optimised usual care, i.e., provision of written information on ACP (an abbreviated version of the information brochure) at the beginning of the study.

After completion of the data collection, interested nurses of the home care services in the control group will be offered a 1-day workshop on ACP.

### Primary outcome

The primary outcome is patient activation, assessed by the Patient Activation Measure (PAM-13-D) [34] at 12 months. The PAM-13 is a valid and reliable instrument which measures the degree to which individuals take an active role in managing their own health, the corresponding health care and its consequences, and the extent to which they feel competent to fulfil that role [35]. The German version (PAM-13-D) has shown to be a reliable and valid measure of patient activation [36, 37]. Each item can be answered with one of four possible response options, which range from “disagree strongly” [1] to “agree strongly” [4]. One item (no. 4) has a fifth response option, namely “I do not take medications”. Raw scores are added up (range 0–100) with higher scores indicating more participation. The PAM-13-D will be assessed via face-to-face interviews by trained study assistants who are blinded to the group allocation of clusters.

### Secondary outcomes

The secondary outcomes are the proportion of participants with ADs, self-reported health related quality of life (VR-12 with 12 items) [38, 39], anxiety and depression (HADS with 14 items) [40], number of hospitalisations, proportion of participants being institutionalized, mortality, and ACP engagement with four items on readiness to pass the ACP process [41] (Table 2). Data measurement will be conducted at baseline (t0), after 6 months (t1) and after 12 months (t2). Baseline data will include age, sex, family situation, amount of health care services used, selected comorbidities, hearing capacity, vision, mobility, and functional status. Most of these data will be assessed in face-to-face interviews with the patients at their homes. Data routinely documented by the respective home care services will be collected during visits at the home care service.

**Table 2 Tab2:** Study outcomes/variables, measurement tools and data collection schedule

Outcome/ variable	Measured by	Validated version*	Baseline	6 months (t1)	12 months (t2)	Assessed by
Patient activation (primary outcome)	Patient activation Measure (PAM-13) [42]	German version [36]	✓	✓	✓	RA – at home visit
ACP behaviour	Patient engagement survey [41]	English version [41]	✓		✓	RA – at home visit
Anxiety and depression	Hospital anxiety and depression scale (HADS) [40]	German version [43]	✓		✓	RA – at home visit
Self-reported, health-related quality of life	Veterans Health Administration (VR-12) [38, 39]	German version [44]	✓		✓	RA – at home visit
Deaths, hospitalization, institutionalisation	Own questions	n.a.	✓	✓	✓	RA – at home care service & home visit
Proxy/Family involvement**	Audit of ACP discussion	n.a.	✓			Nurse facilitator
Sociodemographic & clinical data, hearing capacity by RAI-NH [45] & vision	Own questions	n.a.	✓			RA- at home care service & home visit
GPs involvement	Own questions	n.a.	✓	✓	✓	
Physician visits, formal & informal care	Own questions	n.a.	✓		✓	RA – at home visit
Healthcare preferences	Hypothetical scenarios	Adapted German version [46]***	✓		✓	RA – at home visit

*****all instruments were pretested in a German version in the pilot study**; ****intervention group only; ******* adapted version of the Life-Support Preferences Questionnaires and Emanuel Medical Directive, which will be validated in the STADPLAN study within a limited subgroup (*n* = 120); *RA* Research assistant, *RAI-NH* Resident Assessment Instrument for Nursing Homes

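### The advance-directive endpoint is worded two ways, has no row in the measurement schedule, and no use of directive status at entry is fixed, so read literally it dilutes the effect the objective asks about

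*Protocol article*

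**What the plan says.** The protocol article describes the endpoint in three places.

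- Objective: "Further aims are to assess the intervention’s impact on patients’ ACP engagement as well as prepared AD forms, hospitalisations and institutionalisations".
- Abstract, Methods: "Secondary endpoints include ACP-engagement, proportion of prepared advance directives, number and duration of hospitalisations".
- Methods, Secondary outcomes: "The secondary outcomes are the proportion of participants with ADs, self-reported health related quality of life".

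The first two speak of directives that are prepared. The third, which is the list of outcomes in the Methods, speaks of participants who have one and does not limit this to directives made since baseline.

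The patient eligibility section does not exclude AD holders; it ends "No further exclusion criteria will be applied". On prevalence, the abstract's background says only "ACP is still uncommon in Germany and only few people have advance directive forms", and the Background section adds that it has been rising. No figure is given.

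The Secondary outcomes section refers to Table 2 for instruments, time points and assessors. The table has ten rows. Every other secondary outcome named in that sentence is covered by one; ADs are not. The same section states, for data measurement in general, time points at baseline, 6 months and 12 months.

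Under Data analysis, adjustment for baseline values is written out for the PAM-13-D only. Secondary endpoints are to be analysed with mixed models that allow for clusters or repeated measurements.

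**The concern.** Whether counselling leads people to prepare a directive is a question about new events after enrolment. The share of participants who hold a directive is a prevalence. The two agree only if nobody holds an AD at entry. Anyone who does is a success in either arm whatever the intervention achieves, so that participant adds to the denominator and the variance but cannot add to the difference.

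The AD result is one of the most concrete outcomes of an ACP programme. If the definition stays open, two analysts could report different quantities under the same endpoint name. If the literal wording is followed without regard to status at entry, a real effect on preparing ADs may look small or be missed.

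**Working it through.** **Inputs from the article.** 32 clusters with 960 participants, allocated 1:1, hence 480 per arm; 30 per cluster; ICC 0.05; two-sided 5% level.

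**The article's own figure.** A t-test with d = 0.35 and 90% power needs 172.5, rounded up to 173 per group. Design factor: 1 + 29 × 0.05 = 2.45. Then 173 × 2.45 = 423.9, and 423.9 / 30 = 14.1, rounded up to 15 clusters per group; 32 × 30 = 960. The sample size reproduces. It concerns the primary outcome; no figure is given for ADs.

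**Assumptions, not in the article.** Baseline AD prevalence p0 of 0, 10, 20 or 50%. Among participants without an AD at entry, a proportion a = 10% (control) and b = 25% or 20% (intervention) prepare one by 12 months. Existing ADs are kept, follow-up is complete, and the ICC chosen for the primary outcome also applies to ADs.

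**Endpoint as literally worded (has an AD at 12 months).**

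- Proportions: p0 + (1 - p0)a and p0 + (1 - p0)b.
- Difference: (1 - p0)(b - a).
- Effective size: 480 / 2.45 = 195.9 per arm.

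**New AD among those without one at entry.**

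- Difference: b - a, whatever p0 is.
- Size: 480(1 - p0) per arm, divided by 1 + (30(1 - p0) - 1) × 0.05. This gives 432 / 2.30 = 187.8 at p0 = 10%, 384 / 2.15 = 178.6 at 20% and 240 / 1.70 = 141.2 at 50%.

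**Power.** Φ[(difference - 1.96 × SE0) / SE1], with SE0 from the pooled proportion and SE1 from the separate proportions.

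Example, p0 = 20%, 10% vs 25%:

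- Literal endpoint: 28% vs 40%; SE0 = √(0.34 × 0.66 × 2 / 195.9) = 0.0479; SE1 = √((0.2016 + 0.2400) / 195.9) = 0.0475; (0.12 - 0.0938) / 0.0475 = 0.55, power 71%.
- New ADs: SE0 = √(0.175 × 0.825 × 2 / 178.6) = 0.0402; SE1 = √((0.0900 + 0.1875) / 178.6) = 0.0394; (0.15 - 0.0788) / 0.0394 = 1.81, power 96%.

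| p0 | Difference, literal (10% vs 25%) | Power, literal | Power, new AD | Difference, literal (10% vs 20%) | Power, literal | Power, new AD |
|---|---|---|---|---|---|---|
| 0% | 15.0 points | 98% | 98% | 10.0 points | 79% | 79% |
| 10% | 13.5 points | 87% | 97% | 9.0 points | 56% | 78% |
| 20% | 12.0 points | 71% | 96% | 8.0 points | 40% | 76% |
| 50% | 7.5 points | 33% | 92% | 5.0 points | 17% | 65% |

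The shrinkage by (1 - p0) holds for any new-AD rates, provided existing ADs are kept. The power figures depend on the assumed rates and ICC.

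**The case against.** No sentence says that pre-trial directives count as successes. The abstract's own endpoint uses the word prepared, so the documents show an ambiguity, not a decision. This stands, and the point is worded accordingly.

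AD status at 12 months in everyone randomised is also a legitimate intention-to-treat endpoint. The Background describes regular updating of directives as part of ACP, and the Intervention group section says that completing AD forms is not part of the intervention. This stands too: prevalence is acceptable, provided that status at entry is used.

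The magnitude rests on assumed inputs. If few means about 10%, the loss in the 10% vs 25% case is moderate (87% against 97%), though it is larger with 10% vs 20% (56% against 78%).

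A reader might go further in four ways that the article does not support:

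- That old and new directives cannot be separated. The general statement of measurement at baseline, 6 and 12 months follows directly on the list of secondary outcomes. It is not tied to ADs, but it leaves collection at baseline open. A repeated-measures model for secondary endpoints could also use it.
- That AD status is not collected at entry because it is absent from the list in "Baseline data will include age, sex, family situation, amount of health care services used, selected comorbidities, hearing capacity, vision, mobility, and functional status". That list also omits the PAM-13, HADS and VR-12, all of which Table 2 ticks at baseline, so the absence proves nothing.
- That the patient interview misses those who die. No source for AD status is named, and routine data are also collected at the home care service.
- That chance imbalance in prior directives is a further harm. It is already part of the sampling variance behind the power figures, and a cluster-adjusted test keeps its error rate. Counting it again would double the charge.

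**Conclusion.** The point holds as an inconsistency in definition and schedule, with an avoidable loss of power. The endpoint carries two wordings. The literal Methods wording includes directives that predate the trial. The table cited for secondary outcomes leaves this one out. No use of AD status at entry is fixed. The gap in Table 2 is not merely detail left to a fuller document, since the article prints the schedule and refers to it for these outcomes.

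The comparison is unbiased under randomisation. What is lost is effect size, by the factor (1 - p0), and precision. Across assumed p0 of 10 to 50%, power is 87% to 33% instead of 97% to 92% for 10% vs 25%, and 56% to 17% instead of 78% to 65% for 10% vs 20%. If p0 is close to zero the loss is negligible; the article does not let the reader tell. The endpoint is secondary, and the primary analysis and sample size are unaffected.

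**What to change.** Use one definition in the abstract, Objective and Secondary outcomes, and let it take account of AD status at entry. Either of these would do:

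1. A new AD between baseline and 12 months among participants without one at baseline, with updates of existing ADs and overall prevalence reported alongside.
2. AD status at 12 months in all participants, adjusted for AD status at baseline in the cluster-adjusted model.

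Add an AD row to Table 2 with time points, source (home visit and home care service record) and assessor. According to Trial status, baseline was completed in January 2020 and follow-up runs to January 2021. If status at entry was not recorded, ask for the date of the directive at follow-up and classify it as pre-existing or new.

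The cost is one or two questions and one table row, using visits that already take place. The first option has a smaller denominator. Where status at entry has to be reconstructed, either option relies on recalled or recorded dates, which may be wrong.
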